## Abstract

Today, university students face study conditions that increase the risk of sedentary behavior, unhealthy eating, and the likelihood of stress, anxiety, and depression. Although the situation has likely worsened in recent months due to the COVID-19 pandemic, even in the pre-Corona era, several investigations have demonstrated that the students’ health behaviors could increase the incidence of metabolic risk factors and non-communicable diseases, however, further and detailed information is needed to develop tailored counter-strategies. Therefore, in the present survey, the current health status of students at the Albert-Ludwigs-Universität Freiburg (ALU) will be recorded by various questionnaires. In addition, barriers that could potentially influence their health behavior will be identified, and information on the use and awareness of existing health services will be obtained in order to derive concrete needs for further health promotion activities. The study is designed as a monocentric and prospective study at the ALU; the survey of students’ situation and needs assessments will be conducted in the areas of nutrition, exercise, relaxation and stress reduction, self-management, psychosocial health and socio-demographic correlations via an anonymous and self-administered online questionnaire. Subsequently in two-year intervals, the survey will be repeated. Data will be collected over a period of 4 years. One goal of this survey is to gain more insight into the health situation of university students; another goal is to use the knowledge gained to integrate holistic health measures into the university landscape in a structured and sustainable manner. These health measures will be implemented by using the newly developed student health care management at the ALU (www.sgm.uni-freiburg.de). Every two years, after evaluation of the surveys, the effect of the health measures can be checked and adjusted.

**Trial registration:** ETK: 20–1082; DRKS-ID: DRKS00024088.

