### 4.2 Questionnaire survey

At the start of the study and subsequently at two-year intervals until 2026, situation and needs analyses will be conducted using validated and evaluated questionnaires. Data will be collected via an anonymous and self-administered online questionnaire via Social Science Survey [SoSci Survey] [38]. All questionnaires applied have been validated and have already been employed in various studies addressing comparable issues. No modifications have been made to the questionnaires in the context of the present investigations that would necessitate a re-validation.

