## 6. Data management and data protection

Data management will be carried out in accordance with Good Clinical Practice (GCP) requirements and the provisions of the European Union Data Protection Regulation (EU-DSGVO). The data for the study evaluation will be collected per student via an online questionnaire using SoSci Survey. Large-scale scientific survey projects using SoSci Survey have been successfully conducted for the realization of such studies for many years. After data collection, SoSci Survey exports the data correctly, completely and immediately in the form of a spreadsheet to a password-protected computer and automatically deletes it irrevocably from the SoSci Survey server after 3 months. No one except the study director and the participating researchers (page 1) are allowed to view the password-protected and encrypted spreadsheet.

All student-relevant study data will be stored anonymously. Name, private address, personalized e-mail address, matriculation number or other identification numbers of students will not be requested. Merely a random number will be assigned to each student. Only after the students have voluntarily sent their number to the scientists involved (e-mail: [contact]), will it be possible to assign the person at great expense in terms of time, cost and manpower.

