## 7. Discussion

Previous research has shown that university students are increasingly likely to have unhealthy lifestyles and are exposed to growing stress in their studies as well as in their daily lives. Particularly in the areas of physical activity [6], nutrition [7], stress [8] and self-management [9] as well as psychosocial behavior of students [10], it has been clearly shown that there is a need for lifestyle and behavioral improvement. At the moment, this situation is further exacerbated by the current COVID-19 pandemic [66]. The health situation of students at the ALU Freiburg has not yet been surveyed in any study, which reveals the need for an up-to-date situation and needs analysis.

The primary objective of this survey is the collection of data on health behavior patterns with regard to the above-mentioned items as well as an assessment of life circumstances and the overall association of these findings with sociodemographic data of students at the ALU Freiburg. Therefore, the situation and needs analyses will be carried out at the beginning of the project and subsequently every two-years.

Based on the results, the aim of ALU Freiburg is to establish a university-wide network in the field of student health promotion and thus to establish a sustainable student health management (SGM– www.sgm.uni-freiburg.de). In the long term, the aim is to create an environment for students that promotes both, health and good performance in their studies.

Through the repetition of surveys every two years, the health situation of the students will be repeatedly recorded in order to subsequently develop new health offers dependent on the results of the actual needs assessment. Consequently, this measure makes up an important part of the overall Student Health Management (SGM) project.

In conformity with the current body of literature on student health, it is equally apparent that in some outcome variables, there is a strong variation regarding gender as well as between faculties [12]. Thus, the study aims to collect as diverse information as possible on the age, gender, and program affiliation of students in order to create tailored programs for different student groups.

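### The abstract says the effect of the health measures can be checked every two years, but repeated anonymous waves at one university without a comparison group can show only change between waves

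*Protocol article*

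**What the plan says.** The abstract closes with the statement that every two years, once the surveys have been evaluated, "the effect of the health measures can be checked and adjusted". The same abstract says "Data will be collected over a period of 4 years", and section 4.2 fixes the waves: "At the start of the study and subsequently at two-year intervals until 2026".

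On the design, section 4.2 says "Data will be collected via an anonymous and self-administered online questionnaire". Section 6 adds that "matriculation number or other identification numbers of students will not be requested" and that "Merely a random number will be assigned to each student". A person can be assigned to a record only if the student chooses to send that number in. Section 5 calls the study exploratory and monocentric and the respondents an opportunity sample. Section 7 describes the intended health-promotion network as university-wide.

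On background influences, section 7 says of students' health: "At the moment, this situation is further exacerbated by the current COVID-19 pandemic". Section 2.1 makes COVID-19 stress a target variable. Section 1 reports declining activity and more sitting over the past decade, and rising alcohol and drug use among students.

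Section 7 also states the purpose of the repeat surveys more modestly: they record the health situation again so that new offers can be developed from the results.

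**The concern.** Checking the effect of a measure means comparing what happened with what would have happened without it. Nothing in the article supplies the second half of that comparison. Between two waves two years apart, the measures change, and so do the enrolled student body, the set of people who choose to respond, the long-term trends and the state of the pandemic. A before-after difference adds all of these together.

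The abstract ties the check to adjustment of the programme. If a wave difference is taken for an effect, measures may be kept because the background improved, or dropped because it worsened, whatever they did themselves.

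**Working it through.** **1. What attribution would need, set against what is described**

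| Needed to separate effect from background | What the article describes |
|---|---|
| Concurrent unexposed group, or staggered introduction | One university (section 5); no staggered introduction by faculty or period. Surveys at other universities are used to compare results (section 2) and are not described as concurrent or repeated. |
| The same people followed, or a stable sampling frame | Anonymous voluntary waves (sections 4.2 and 6); a random number is assigned, with no statement that it carries over; an opportunity sample (section 5), recruited partly through the programme's own social platforms and its kick-off event (section 3.3). |
| Stable background | Long-term trends in activity, sitting, alcohol and drugs (section 1); pandemic influence (abstract, sections 2.1 and 7). |
| An analysis of the effect | Section 5 lists tests for guideline attainment, gender and faculty, then regression, correlation and structural equation models. None is described as a comparison between waves. |

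None of the four is present in a form that supports attribution.

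**2. The plan's own figure**

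The only stated sample size is more than 500, given in section 3.2 as more than 2% of students. Check: 12,908 + 11,483 = 24,391, and 0.02 × 24,391 = 487.8, so about 500 reproduces. This size serves description of one wave. No between-wave effect size is stated.

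**3. Illustration: how often background drift alone looks significant**

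Inputs: n = 500 per wave (section 3.2, taken as exactly 500); two-sided α = 5% (section 5); baseline p₁ = 30.6% (section 1, a literature figure for depression among students, used here as an assumption and not a Freiburg estimate). The measures are assumed to have no effect, and the drift sizes are assumptions.

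With p̄ = (p₁ + p₂)/2, the probability of a significant difference is

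Φ{ [ |p₁ − p₂| − 1.96 √(2 p̄(1 − p̄)/n) ] / √( [p₁(1 − p₁) + p₂(1 − p₂)]/n ) }.

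For a fall of 8 points: p₂ = 0.226 and p̄ = 0.266. The first square root is 0.02795 and the second 0.02783. Then (0.080 − 1.96 × 0.02795)/0.02783 = 0.906, and Φ(0.906) = 0.82.

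| Background fall | Baseline 30.6% | Baseline 50% (assumed) |
|---|---|---|
| 3 points | 18% | 16% |
| 5 points | 42% | 35% |
| 8 points | 82% | 72% |
| 10 points | 95% | 89% |

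As a cross-check, the difference detectable with 80% power is (1.96 + 0.84) × √(2 × 0.306 × 0.694/500) = 0.082, about 8 points.

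For a score, a background shift of δ standard deviations gives Φ(δ/√(2/500) − 1.96). For δ = 0.1 this is Φ(1.58 − 1.96) = 35%; for δ = 0.2, Φ(3.16 − 1.96) = 89%.

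**4. Sample size does not help**

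The bias equals the background shift and does not depend on n. With 1,000 per wave, the same formula for a 5-point fall from 30.6% gives (0.050 − 1.96 × 0.02010)/0.02007 = 0.53, so 70% instead of 42%.

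**The case against.** The strongest reply is that no effect analysis is planned. The clause is the last sentence of the abstract's description and says only that the effect can be checked. It is not an objective in section 2, a target variable or an analysis in section 5, and section 7 makes the weaker statement. The study calls itself exploratory and mainly descriptive. This stands as a limit on the size of the point: a stated claim is at fault, and no planned test is. It does not remove the point, because the sentence is in the current text and says what the results are for.

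The pandemic was also not ignored: section 2.1 collects infection status and pandemic stressors. That helps to describe the influence but does not replace a comparison group.

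A reader might infer more than the documents support:

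- **That later waves will improve anyway as the pandemic recedes.** No source for this is given. Section 1 reports worsening long-term trends, so the direction of drift is unknown. The pandemic-era start is itself inferred, from 2026 minus 4 years, about 2022; no start date is given.
- **That the random number is known not to carry over.** The article is silent; absence of linkage is an inference.
- **That independent-sample tests will be misused on overlapping waves.** Section 5 names those tests for characteristics such as gender and faculty, not for waves.
- **That no student will be unexposed.** Section 7 speaks of a university-wide network but also of programmes tailored to groups. What is missing is a planned comparison.
- **That any 8-point drift would be significant.** At about 80% power, roughly one in five would not be.
- **That a self-generated linking code would solve it.** Two independent draws of 500 from 24,391 share about 500 × 500/24,391 = 10 students, before turnover and unmatched codes. Comparing change in users and non-users of services would also be self-selected, and a code touches the anonymity on which presumed consent rests (section 4.1).

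**Conclusion.** The point holds as a mismatch between a stated claim and the design. The repeated surveys can monitor students' health over time, but they cannot show that a change came from the measures. This rests on what the article describes: one university, self-selected respondents, no concurrent or staggered comparison, no stated linkage, and background influences that the article itself reports.

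The size is conditional. Under the assumed 500 per wave and no effect of the measures, an 8-point background fall would be significant in about 72% to 82% of cases over the two assumed baselines, against a nominal 5%. The actual drift at this university, and its sign, are not known from the documents. The descriptive objectives are unaffected.

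**What to change.** 1. In the abstract, replace the statement that the effect of the health measures can be checked with one that change in students' health between waves can be monitored, in line with section 7.
2. Add a sentence that change between waves will not be interpreted as an effect of the measures.
3. Optionally, hold each wave in the same weeks of the semester. Several instruments look back only over the last two weeks to a month (sections 4.2.2, 4.2.3 and 4.2.5), so this makes waves more comparable. It would not permit attribution. The article does not say when in the semester the waves fall, so this is a precaution and not a correction.

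Items 1 and 2 cost only wording; item 3 costs a scheduling constraint. The downside is that the study claims less. No new data collection or linkage code is needed.

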## 1. Introduction

In recent years, curricula at many universities in Europe have changed on several levels [1]. Above all, there is a development towards a more rigid curriculum with greater time pressure [2].

Along with the COVID-19 pandemic in spring 2020, face to face instructions ended and teaching and learning had to shift to digital and online formats [3]. In addition, hygiene and social contact regulations have affected the students’ social and academic life [4]. University students are thus increasingly exposed to conditions that resemble the modern world of work with its enhanced workload and exposure to stress [5]. Research over the past several decades in the areas of physical activity [6], nutrition [7], relaxation and stress reduction [8], self-management [9] as well as psychosocial behavior [10] of students has demonstrated a clear need for lifestyle and behavioral improvements.

Compared to all other age groups, university students have had the greatest decline in physical activity and the greatest increase in sedentary behavior across the past decade [6, 11]. Only 20–30% of students in Germany meet the World Health Organization (WHO) guidelines for physical activity [12, 13]. In this context, the differences between the individual faculties at Universities are striking [12]. In addition, there is an increasing trend towards sedentary behavior, especially among female students [14, 15].

Alongside a physically active lifestyle, a healthy and balanced diet contributes significantly to the prevention of chronic diseases such as type 2 diabetes and cardiovascular diseases [7, 16]. In contrast, an unhealthy diet promotes the risk for non-communicable diseases (NCD) and increases NCD health related risk factors even at younger ages [17]. If one compares the food intake in Germany with the recommendations of the German Society for Nutrition [DGE], one finds an excessive consumption of foods of animal origin. In contrast, the consumption of vegetables corresponds to only about one third of the recommendations [18]. Students, in particular, rarely meet recommendations for fruit and vegetable consumption and also deviate unfavorably from recommendations in other food categories [19, 20].

Beginning a university education is accompanied by major changes in life circumstances, often involving significant challenges and changes in students’ lives, such as moving out of the parental home, living alone, identity crisis or an altered daily routine [21]. In Germany, 53% of students feel exposed to a high stress level and 42% to a medium stress level. According to Herbst et al. (2016), female students are more stressed than male students and the type of university or the study program also has an impact on stress experience [22]. Psychological stress often implies reduced mental health and leads to lower performance [23, 24].

Due to the heavy workload with too many courses, exams, and study hours, approximately 50% of students state that their resources and subjective stress limits are exceeded [25]. Good self-management has been shown to have a significant positive impact on greater work and life satisfaction [26] as well as academic performance [27]. Interestingly, female students show higher self-management skills compared to male students. This shows that a differentiated view with separation into genders, study programs or university faculties is necessary to gain a better understanding of the required countermeasures [26].

Over the last few years, alcohol and drug use among students has increased significantly [28]. Students have a remarkably higher alcohol consumption compared to the general population and are more prone to abusive consumption patterns [29]. Male students in particular have more problematic usage patterns compared to female students [30, 31]. Abuse of illicit drugs is also particularly prevalent among young people [32]. Accordingly, students are considered a risk group for problematic consumption behavior, which can lead to various problems at the physical, social, and psychological level [33].

Among students, mental disorders are relatively common. Based on the World Mental Health Survey, Auerbach et al. (2016) reported that 20% of students worldwide have had some form of mental or anxiety disorder or depression in the past 12 months [10]. The prevalence of anxiety disorders peaks globally at age 20–24 years and varies widely by gender and international regions [34]. The reported prevalence of depression among college students varies from 10% to 85%. However, the weighted prevalence of 30.6% is significantly higher than for the general population [35]. The wide range of results shows that we need more diverse research on this question.

The current health situation of students at ALU Freiburg has not yet been surveyed in any study. The aim of the information obtained is to structure holistic health-promoting measures and integrate them into the university landscape in a structured and sustainable manner.

## 2. Project objectives

The primary objective of the situation and needs analysis is the collection of data on health behavior patterns with regard to physical activity, nutrition, relaxation and stress reduction, self-management, psychosocial health as well as life circumstances and the overall relationship with sociodemographic data of students at the ALU Freiburg. The results will be compared with student surveys from other universities but more importantly, the data will be aligned with national and international guidelines to determine if or in how far they are met by the students. As a secondary goal, barriers that influence health will be identified, and information will be obtained on the use and awareness of preexisting health services at ALU or externally. The need for health interventions is derived from both primary and secondary goals of this survey (cf. below).

From the knowledge gained, health measures will be structured and sustainably integrated into the university landscape with the aim of aligning the university with health promotion and disease prevention of its students. These goals will be realized in the respective categories via the following primary and secondary target variables.

### 2.1 Primary target variables

1. Physical activity: The primary outcome measure is the achieved Metabolic Equivalent (MET)-minute count per week in strenuous and moderate activity. This will be compared to WHO guidelines on health-promoting physical activity (600 MET minutes per week). In addition, the average sitting time in hours per day will be quantified. These primary outcome measures will be examined for gender and faculty differences and target groups with below-average physical inactivity and high sedentary behavior identified.

2. Nutrition: The main target variable is the summed value of all 10 identified food categories summarized as the Healthy Eating Index of the National Eating Survey II (HEI-NVS II index). This indicates whether the DGE recommendations of healthy eating are met (≥ 100 points). These primary outcome measures will also–as all following target variables—be examined with respect to gender and faculty differences to identify target groups with a higher-than-average unhealthy eating pattern. Thus, target groups with above-average unhealthy eating behavior can be detected.

3. Relaxation and stress reduction: The primary outcome measure is stress experience as measured by the summed score of the Perceived Stress Scale-10(PSS-10). This will be applied to examine how many students have a moderate to high stress experience (PSS-10 sum > 13). The 5 coping strategies of the Stress and Coping Inventory (SCI) represent another outcome measure of the primary objective. They are each assigned to a below-average or above-average performance level in order to determine target groups with above-average stress experience.

4. Self-management: The main target variable is the self-management competence of the students, measured by the sum value of the SMST. It examines the number of students who have mediocre to very poor self-management skills (SMST sum score < 13). As such, the identification of target groups with below-average self-management skills is made possible.

5. Psychosocial health, consisting of a) alcohol and drug use, b) depression, c) anxiety disorders, and d) sleep disorders:

(a) Alcohol consumption, as assessed by the AUDIT sum score, will be the primary outcome. The extent to which students exhibit problem drinking patterns, symptoms of alcohol dependence and characteristics of risky consumption (AUDIT sum > 11) will be addressed.(b) Harmful drug use, quantified by the sum score of the DUDIT (men: ≥ 6; women: ≥ 2), is another outcome variable of the primary target.(c) In addition, the prevalence of depression will be surveyed (PHQ-9: cut-off ≥ 10). The severity of a possible depression will be gauged by a dimensional assessment of the questionnaire (10–14 mild depression; 15–19 moderate depression; 20–27 severe depression).(d) Generalized anxiety disorder, as scored by the GAD-7 (cut-off ≥ 10), is another primary outcome criterion. Specific severity (mild, moderate, severe) of generalized anxiety disorder will be graded by the dimensional score of the GAD-7.(e) Insomnia represents the final primary outcome measure. Using the ISI(cut-off ≥ 10), the extent to which students suffer from insomnia will be quantified.

6. Covid-19-Infection: The COVID-19 pandemic has had a significant impact on students’ lives across multiple domains. In addition to exploring inquiries regarding their infection status, frequency, and potential symptoms associated with "Long-Covid," we will utilize the COVID-19 Student Stress Questionnaire (CSSQ) to assess the stressors experienced by students throughout and following the pandemic. This questionnaire has been specifically designed and evaluated to assess COVID-19-related sources of stress among university students and is therefore well suited to address related problems [36].

